## Abstract

**Background:**

High sodium intake is a significant public health problem in the United States. Interventions that lower sodium intake can decrease blood pressure and improve cardiovascular outcomes. Restaurants and grocery stores are prime targets for intervention with about 77% of all sodium intake in the average US diet coming from processed and restaurant foods.

**Objective:**

This study proposes that a mobile app intervention that promotes low-sodium alternatives at grocery stores and restaurants will reduce dietary intake of sodium and improve confidence following a low-sodium diet in hypertension.

**Methods:**

In this single-center, prospective, open-label study, patients will be randomized to a mobile app or usual care for 8 weeks. We will randomize 50 patients (age>18 years) diagnosed with hypertension and on antihypertensive therapy for at least 3 months in a 1:1 manner stratified by gender. Study subjects will receive the mobile app, LowSalt4Life, or usual dietary advice for 8 weeks. LowSalt4Life provides a multifaceted intervention based on just-in-time contextual tailored messages at grocery stores and restaurants. The primary endpoint is the change in the estimated 24-hour urinary excretion of sodium from spot urine. Secondary outcomes include change in the sodium content of the food frequency questionnaire, confidence in following a low-sodium diet, urine chloride and creatinine dipsticks, and blood pressure.

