### Aim and Hypothesis

The LowSalt4Life Trial will study the effectiveness of a newly developed mobile app that provides mobile phone sensor-based contextual push messages related to following a low-sodium diet. We will randomize patients with hypertension to the mobile app or standard of care for 8 weeks. From baseline to 8-week follow-up, we will assess the impact of the mobile app on the dietary intake of sodium (measured by 24-hour dietary recall and 24-hour urinary sodium excretion) and confidence following a low-sodium diet, measured by the Self-Care Confidence in Following a Low-Sodium Diet Scale (SCFLDS). We hypothesize that the group randomized to the mobile app will demonstrate improvement in these measurements compared with the control group (Table 1).

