### Study Subjects

We will enroll 50 patients aged >18 years diagnosed with hypertension and on antihypertensive therapy for at least 3 months. Patients will be excluded if they have CKD, heart failure, SBP >180 mm Hg, diastolic blood pressure >110 mm Hg, insulin-requiring diabetes mellitus, or are taking a loop diuretic, corticosteroid, or nonsteroidal anti-inflammatory medication. CKD is defined as known kidney damage (structural or functional abnormalities) or estimated glomerular filtration rate of <60 mL/min/1.73 m^2^ (CKD stage 3, 4, or 5). Initially consented participants will complete the Block Food Frequency Questionnaire (NutritionQuest) [21], and those with the estimated baseline sodium intake <2300 mg/day will be excluded before randomization.

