### Outcomes

The Automated Self-Administered 24-Hour Dietary Recall (ASA24), developed by the National Cancer Institute for dietary research, will be used to estimate the dietary sodium intake during the trial. The ASA24 is an electronic 24-hour recall website that allows patients to self-administer the survey in a user-friendly manner. The ASA24 allows researchers to send the survey at defined intervals and automatically performs a dietary analysis by converting the dietary recall data into nutrient information based on the Food and Nutrient Database for Dietary Studies. In order to provide a detailed interview, the website includes a meal-based quick list, meal gap review, review of forgotten foods, a final review, and a question about whether the day’s intake was usual or not. In this study, we will obtain the sodium content per day from the Food and Nutrient Database for Dietary Studies-based sodium content analysis completed by the ASA24 website. The ASA24 will be administered at week 0 and 8 of the study (see Figure 2 for details of outcomes).

The most widely used method for monitoring the sodium intake is urinary sodium excretion measured by a 24-hour urine collection. Patients will be instructed to collect all urine voids for 24 hours and return them for analysis for sodium excretion. In addition, the 24-hour urine excretion will be collected at baseline and after 8 weeks. This method is not convenient (eg, difficult to perform collections at work), and some participants may have incomplete urine collections. Owing to these challenges, we will also explore other methods to estimate sodium excretion that would be more practical for use in larger trials.

In addition to the gold standard, the first method to estimate the 24-hour urinary sodium excretion is spot morning urine excretion of sodium. The Kawasaki formula will be used to estimate the 24-hour sodium urinary excretion from a fasting morning urine sample [25]. This approach has been proven to provide a valid estimate of the sodium intake in several patient populations and in large-scale epidemiological studies [26]. Participants will be instructed to fast overnight, void in the morning, and provide us with a second morning urine sample on the day of the assessment. This measurement will be assessed at baseline and after 8 weeks of the study.

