**Figure 2 figure2:**
[figure not shown]
Summary of outcomes in the trial. ASA24: Automated Self-administered 24-Hour Dietary Recall; FFQ: Food Frequency Questionnaire; SCFLDS: Self-Care Confidence in Following a Low-Sodium Diet Scale.

The second method for estimating the 24-hour urinary sodium excretion is with a spot urine sample using chloride and creatinine dipsticks. The dipstick method has been validated in patients with hypertension and correlates well with the 24-hour urinary sodium excretion (*r*=.86) [27]. The chloride dipstick is used as a surrogate for sodium excretion. The Quantab chloride dipstick (Hach, Loveland, CO, USA) is placed in a container filled less than halfway with urine. The chloride concentration is determined by observation of the change in color from brown to pale on the dipstick, which is the formation of silver chloride. The creatinine dipstick is similar to the chloride dipstick. The MultistixPro-10LS (Bayer, Elkhart, IN, USA) is a dipstick that includes a color pad for creatinine after it is placed in a container filled with urine. The color pad turns from yellow to green to indicate the creatinine concentration. The predicted 24-hour urinary sodium excretion is calculated on the basis of the 24-hour creatinine concentration calculated using sex, weight, race, and age. This model has been validated and correlates highly (*r*=.93) with 24-hour measurements of creatinine [28]. This measurement will be performed at baseline and after weeks 2, 4, 6, and 8.

The SCFLDS will be used to measure patients’ confidence in following a low-sodium diet. It assesses patients’ confidence in the ability to select and prepare low-sodium foods [29]. The tool consists of 7 items with 4 response options per item. The items ask patients to rate their level of confidence reading food labels, choosing low-sodium food during shopping, choosing low-sodium foods at restaurants, cooking low-sodium foods, choosing low-sodium foods at relatives or friends homes, estimating how much sodium they eat each day, and substituting low-sodium foods for high-sodium foods. The 4 response options are assigned a score of 1-4 (1=not confident; 2=somewhat confident; 3=very confident; 4=extremely confident) and then added for each question. Possible scores range from 7 to 28, and the higher score indicates greater confidence. The SCFLDS will be administered at baseline and after week 8 of the study.

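### The abstract names food frequency questionnaire sodium as the dietary secondary outcome, while the aim and Outcomes section name the ASA24 recall; one instrument should be fixed throughout.

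*Protocol article*

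**What the plan says.** - **Abstract, Methods.** The dietary item among the secondary outcomes is the FFQ: "Secondary outcomes include change in the sodium content of the food frequency questionnaire, confidence in following a low-sodium diet". ASA24 is not mentioned.
- **Aim and Hypothesis.** Dietary sodium is "measured by 24-hour dietary recall and 24-hour urinary sodium excretion". The FFQ is not mentioned.
- **Outcomes.** The ASA24 "will be used to estimate the dietary sodium intake during the trial", and its schedule is explicit: "The ASA24 will be administered at week 0 and 8 of the study". No FFQ administration is described here.
- **Study Subjects.** The Block FFQ is completed after consent, and "those with the estimated baseline sodium intake <2300 mg/day will be excluded before randomization".
- **Figure 2 legend.** Both ASA24 and "FFQ: Food Frequency Questionnaire" are spelled out as abbreviations. The figure itself is not available in the text reviewed.
- **Statistical Approach.** A two-sided t test of change between arms is planned for each outcome. Neither the FFQ nor ASA24 is named.

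**The concern.** Two parts of one article give different instruments for what reads as the same outcome. An FFQ asks about habitual intake and a 24-hour recall about a single day, so they are not interchangeable. Both are self-reported in a trial where participants know their arm, and the General Design section accepts that some outcomes are not objective. If the choice stays open until data are in, the more favourable instrument could become the reported one, and a reader could not tell from the article which was intended.

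The FFQ is also the weaker candidate for a change score. The only FFQ described is the one used to select participants. If that value served as baseline, every enrolled participant would have a baseline of at least 2300 mg/day by construction, and a repeat measurement would be expected to drift down in both arms with no intervention effect. A within-arm summary of that change could be misread.

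**Working it through.** **Step 1. Set the sections side by side.**

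| Section | FFQ | ASA24 / 24-hour recall |
|---|---|---|
| Abstract, Methods | Secondary outcome (change) | Not named |
| Aim and Hypothesis | Not named | Dietary sodium measure |
| Study Subjects | Eligibility screen, cut at 2300 mg/day | Not named |
| Outcomes | Not named | Dietary sodium measure, weeks 0 and 8 |
| Figure 2 legend | Abbreviated; role unknown | Abbreviated; role unknown |
| Statistical Approach | Not named | Not named |

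The abstract promises a change score for which the methods text gives no second time point. The instrument that does have two time points is missing from the abstract. The Block Sodium Screener in the Intervention section is named separately, serves to tailor messages and is not offered as an outcome, so it does not settle the matter.

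**Step 2. What a change from the screening FFQ would look like.** The plan states no figure for this, so there is nothing to reproduce. Inputs:

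- Cut c = 2300 mg/day (Study Subjects).
- Pre-screen FFQ sodium assumed normal with mean μ = 3400 and SD σ = 1200 mg/day. The Statistical Approach gives these values for urinary sodium at baseline; using them for the FFQ before screening is an assumption.
- Test-retest correlation ρ assumed between 0.3 and 0.9. The article gives no value.

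Standardized cut: a = (2300 − 3400)/1200 = −0.917.

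Proportion excluded: Φ(a) = 0.180, about 18%.

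Inverse Mills ratio: λ = φ(a)/(1 − Φ(a)) = 0.262/0.820 = 0.3195.

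Mean after screening: μ + σλ = 3400 + 1200 × 0.3195 ≈ 3783, a rise of about 383 mg.

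SD after screening: σ√(1 + aλ − λ²) = 1200 × √(1 − 0.293 − 0.102) ≈ 933 mg.

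Expected fall on repeat with no intervention effect: (1 − ρ) × 383.

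| ρ | Expected fall in each arm (mg/day) |
|---|---|
| 0.3 | 268 |
| 0.5 | 192 |
| 0.7 | 115 |
| 0.9 | 38 |

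**Step 3. Effect on the comparison between arms.** Screening precedes randomization, so the same term applies to both arms. With true effects τ(app) and τ(usual care), the expected changes are τ(app) − (1 − ρ) × 383 and τ(usual care) − (1 − ρ) × 383. The difference is τ(app) − τ(usual care), and the artefact cancels in expectation.

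**Step 4. Why ANCOVA for the ASA24.** With equal variance at both visits and correlation ρ between them, a change score has variance 2σ²(1 − ρ), and the baseline-adjusted outcome has σ²(1 − ρ²). The ratio of the second to the first is (1 + ρ)/2, which does not exceed 1. Apart from one degree of freedom for the covariate, adjustment is therefore at least as precise as the planned t test of change. The week-0 ASA24 it needs is already collected.

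**The case against.** **The abstract may not exclude ASA24.** Its list of secondary outcomes is introduced as non-exhaustive, and it also omits the measured 24-hour urine collection that the Outcomes and Statistical Approach sections plan. Both dietary measures may be intended. This is fair, but it does not remove the disagreement: the aim and Outcomes text omit the FFQ altogether, and no section ranks the two.

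**Figure 2 may settle it.** The Outcomes section refers to that figure for detail, and its legend lists both instruments. The figure could give the FFQ a role and a schedule, so it cannot be said that a week-8 FFQ is absent from the plan, only that the text describes none. The wording of the abstract, aim and Outcomes would still need to agree.

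**The screening FFQ may not be the baseline for a change score.** The text does not say so outright. It does call the screening value the estimated baseline intake and describes no other FFQ, so this is the natural reading, but it is not certain.

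**A reader might infer that the 2300 mg/day cut biases the app-versus-usual-care result or spoils its variance.** The documents do not support this. Screening comes before randomization and the planned test compares change between arms, so the expected fall cancels. Selection narrows the baseline spread in both arms alike, and no harm to the validity or power of the t test has been shown.

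**A reader might also set the illustrated fall against the 100 mg usual-care decrease in the Statistical Approach.** That decrease concerns urinary sodium, not FFQ intake, so the two are not comparable. At a correlation of 0.9 the fall would in any case be only 38 mg.

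**Conclusion.** The inconsistency stands on the text alone. The abstract gives FFQ sodium as the dietary secondary outcome, the aim and Outcomes section give the ASA24 recall, and the statistical text does not decide between them. The consequence is limited: it concerns a secondary outcome, and the primary urinary endpoint is untouched.

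Regression to the mean is a supporting reason to prefer ASA24, not a separate flaw in the randomized comparison. Its size, about 40 to 270 mg/day within each arm, depends on a normal pre-screen distribution, on urinary values borrowed for the FFQ, on an assumed correlation of 0.9 to 0.3, and on the screening value serving as baseline. It should be read as an illustration. ASA24 is not wholly immune, since it may correlate with the screening FFQ, but it is not the measurement on which participants were selected.

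**What to change.** 1. Name ASA24 sodium, week 0 to week 8, as the dietary-intake secondary outcome in the abstract, aim, Outcomes and Statistical Approach, and make Figure 2 agree.
2. In the Statistical Approach, compare week-8 ASA24 sodium between arms by ANCOVA with the week-0 ASA24 value as covariate, in place of a t test of change.
3. State that the Block FFQ is for eligibility. If it is repeated, label it exploratory and report only the baseline-adjusted difference between arms, not within-arm falls from the screening value.
4. Date the clarification and record that it was made before outcome data were examined. The abstract reports 26 of 50 participants enrolled, so at that stage this was still possible.

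The cost is wording in the protocol and, where needed, the registry entry. No new data, visits or participants are required.

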**Results:**

The project was funded in May 2016 until April 2018. This trial is currently enrolling patients. To date, 26 of the 50 patients needed have been enrolled. Results will be available in the Spring of 2019.

**Conclusions:**

This randomized controlled trial will test the efficacy of just-in-time contextual tailored messages through a novel mobile app 8-week intervention on urinary sodium excretion in patients with hypertension. We will address a critical evidence gap in the care of patients with hypertension. If effective, this intervention could be scaled to assess effects on blood pressure and cardiovascular events in hypertension.

**Trial Registration:**

ClinicalTrials.gov NCT03099343; https://clinicaltrials.gov/ct2/show/NCT03099343 (Archived by WebCite at http://www.webcitation.org/735HNzKlQ)

**International Registered Report Identifier (IRRID):**

PRR1-10.2196/11282

## Introduction

### Prevalence and Consequences of High Dietary Sodium Intake

High sodium intake is a significant public health problem in the United States. In a meta-analysis of 177,025 patients, higher sodium consumption was associated with higher risk of stroke (relative risk, RR, 1.23, 95% CI 1.06-1.43) and a trend toward higher cardiovascular risk (RR 1.14, 95% CI 0.99-1.32) [1]. Based on 2005 estimates, high dietary sodium is responsible for 102,000 deaths annually. The current federal guidelines advocate a daily sodium intake of <2300 mg with a further reduction to 1500 mg in persons aged ≥51 years and those of any age who are African American or have hypertension, diabetes, or chronic kidney disease (CKD), while the average sodium intake for all Americans aged ≥2 years is approximately 3400 mg/day [2].

### Effects of Interventions to Lower Sodium Intake

Interventions that lower sodium intake can decrease blood pressure and improve cardiovascular outcomes. The sodium-restricted Dietary Approach to Stop Hypertension eating plan reduced the systolic blood pressure (SBP) by 7.1 mm Hg in adults without hypertension and 11.5 mm Hg in adults with hypertension [3]. In an analysis of the Trials of Hypertension Prevention, participants randomized to low-sodium interventions had a 25% lower long-term risk of cardiovascular disease (RR 0.75, 95% CI 0.57-0.99) [4]. Following the 2003 introduction of a national salt reduction program in England, the 2011 national Health Survey estimated that the population’s sodium intake decreased by ~550 mg/day [5]. During that same timeframe, the population’s SBP declined by 3 (SD 0.3)/1.4 (SD 0.2) mm Hg, which was accompanied by a 42% decrease in stroke mortality (*P*<.001) and a 40% reduction in mortality due to ischemic heart disease (*P*<.001). After extensive adjustment for other potential factors, dietary sodium reduction was identified as the most likely contributor.

From a policy perspective in the United States, reducing sodium intake by 1200 mg/day is projected to prevent 60,000-120,000 coronary heart disease events, 32,000-66,000 strokes, 54,000-99,000 myocardial infarctions, and 44,000-99,000 deaths from any cause on an annual basis [6]. This reduction in sodium intake would also lead to US $10-24 billion savings in the health care system.

### Patients Need Assistance at Grocery Stores and Restaurants

Over half of Americans consume 1-3 restaurant meals per week, and 23% consume ≥4 restaurant meals per week. In addition, the use of prepackaged foods in home meal preparation has increased substantially in recent years. Restaurants and grocery stores are prime targets for interventions, with about 77% of all sodium intake in the average US diet coming from processed and restaurant foods [7,8]. In a recent study on consumer knowledge of sodium intake and food labeling, only half of the over 400 grocery store shoppers could accurately use sodium label information to choose low-sodium food options [9]. The American Heart Association guideline for the dietary approach to prevent and treat hypertension states, “any meaningful strategy to reduce salt intake must involve efforts of food manufacturers and restaurants” [10].

A qualitative study using a focus group that included patients with heart failure proposed 3 primary themes for nonadherence to low-sodium diet as follows: lack of knowledge, interference with socialization, and lack of food selections [11]. Many participants in this study felt they needed more detailed information about a low-sodium diet. They also expressed frustration in eating out at restaurants stating eating out was an obstacle to adhering to their prescribed diet. Finally, patients stated there are limited choices and poor taste of foods with low-sodium content.

### Advancements in Information Technology to Support Reduced Sodium Intake

We are currently witnessing broad social changes in the ways individuals expect to find and use information about their health. According to the Pew Research Center’s Internet and American Life Project, nearly 90% of households now have at least basic internet access, and 70% of households have broadband service [12]. The use of mobile phones has nearly become ubiquitous (with 90% of individuals owning a mobile phone), with a growing majority of individuals (65%) using smartphones [13]. We believe that a mobile app that provides location-based, tailored messages can reduce the dietary sodium intake and increase participants’ confidence in following a low-sodium diet.

The current state for self-monitoring of sodium intake in health information technology (IT) is to have users log all daily dietary intake, a process that requires substantial time and persistence. Patients or the mobile app then calculates dietary sodium intake and reviews it periodically, after the intake has already occurred. Our more proactive approach provides immediately available information on appropriate low-sodium options, as well as the ability to self-monitor the intake of specific high-sodium foods. This type of methodology could provide a significant change in thinking about self-monitoring for diets and nutrition.

From a health IT perspective, the use of contextual geofence-based push notifications is novel. This research will inform how users perceive these messages, which messages they understand most and ultimately if they act on the recommendations of the message. Furthermore, we will appreciate whether patients will accept that a mobile app follows their location to provide dietary recommendations. The research will inform the health IT community how to begin using location-based notifications in a way that does not turn users off to the idea of being tracked by someone.

**Table 1 table1:** Conceptual model for health information technology intervention based on patients’ beliefs.

Patient beliefs about a low-sodium diet and theoretical framework		Intervention
**Lack of knowledge**		
	Attitude	Just-in-time messages based on geofencing technology when a patient enters a restaurant or grocery store provide the knowledge the patient needs to make an informed decision.
	Value proposition in food choices	Associating hypertension and blood pressure to lower sodium intake.
	Self-regulation	Patients will monitor the top 5 high-sodium foods.
**Interference with socialization**		
	Normative belief	Nonobtrusive food options are presented as a push notification when the patient enters a restaurant or scans an item at the grocery store.
**Lack of food selection**		
	Perceived control; Substitution and limitation as a food choice strategy	Several food options are presented that are usual food options at the restaurant and the ability to scan foods at the grocery store. This puts a patient in control of limiting sodium and substituting other low-sodium foods.

